## Methods/Design

### Participants

We aim to enroll 100 preschoolers with ASD who will be recruited from the Child and Adolescence Mental Health Services of Tuscany Region, and from the Unit of Child Psychiatry and the Unit of Child Rehabilitation of IRCCS Stella Maris Foundation (Pisa, Italy). This is a tertiary care University Hospital with a unit, exclusively dedicated to ASD, who receives approximately 250 patients per year (mostly preschool children) for diagnosis and treatment from all over Italy. All children recruited will be assessed at IRCCS Stella Maris Foundation.

The following inclusion and exclusion criteria will be adopted:

Inclusion criteriaage-range: 18–72 months. The interest in assessing the effects of probiotic supplementation in preschoolers with ASD relies on the strong recommendation to lead early treatments in ASD, given the demonstrated positive impact of early interventions on the core symptoms of the disorder [59].ASD diagnosis according to DSM-5 (Diagnostic and Statistical Manual of Mental Disorders-5th Edition) criteria [1]: Participants must have a diagnosis of an ASD as assessed by a senior child psychiatrist with a specific expertise in clinical evaluation of ASD according to DSM-5 criteria before their recruitment in the study.

Exclusion criteria

a. brain anomalies detected by Magnetic Resonance Imaging; b. neurological syndromes or focal neurological signs; c. anamnesis of birth asphyxia, severe premature birth (≤28 gestational weeks) or perinatal injuries; d. epilepsy; e. significant sensory impairment (e.g., blindness, deafness); f. diagnosis of organic GI Disorder (i.e. gastro-esophageal reflux, food allergies, IBD); g. diagnosis of Coeliac Disease; h. special diet (i.e. gluten-free diet, casein-free diet, high-protein diet, ketogenic diet).

The criteria from a. to e. are intended to exclude children affected by not idiopathic forms of ASD or by particular endophenotypes of the disorder as the “ASD plus epilepsy” one. The criteria f. and g. are intended to exclude children with not idiopathic or not functional GI disorders. Children already enrolled in dietetic treatment studies will not be included (criteria h.) given the possible interferences of such diets on GI system during the probiotic/placebo supplementation.

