### Interventions

ASD participants belonging to the two groups (GI and NGI) will be blind randomized 1:1 to regular diet with probiotics or with placebo for 6 months. Therefore, four subgroups will be obtained:Group 1) GI symptoms and probioticsGroup 2) GI Symptoms and placeboGroup 3) Non-GI symptoms and probioticsGroup 4) Non-GI symptoms and placebo

The probiotic preparation selected for this study is a mixture (Vivomixx®), each packet of which contains 450 billions of lyophilized bacterial cells belonging to eight probiotic strains: one strain of Streptococcus thermophilus DSM 24731, three strains of Bifidobacterium (B. breve DSM 24732, B. longum DSM 24736, B. infantis DSM 24737), and four strains of Lactobacillus (L. acidophilus DSM 24735, L. plantarum DSM 24730, L. paracasei DSM 24733, L. delbrueckii subsp. bulgaricus DSM 24734). Vivomixx® is a patented and marketed product and it has been approved for the use in children. This study protocol will require the oral administration of Vivomixx® which is available in a water-soluble formulation that can be dissolved directly in the mouth or in a cold, not carbonated liquid. According to the daily weight-based dose of Vivomixx® and the age and weight range of ASD children who will be recruited in the study, the protocol posology will be two packets a day (900 billions bacteria) in the first month of treatment and one packet a day (450 billions bacteria) in the following 5 months of treatment.

The treatment will be administered to children at home by their parents/legal guardian during the 6 months of the treatment protocol. A treatment duration of 6 months has been chosen in order to warrant a good colonization of the gut, that requires 2–3 weeks on average, and its maintenance for a period of time long enough to determine possible significant clinical changes.

The placebo’s packaging and organoleptic characteristics will be identical to the probiotic ones. Each packet of placebo will contain 4.4 g of maltose and silicon dioxide.

It will not be possible to modify allocated interventions for a given trial participant. Participants will discontinue interventions as a consequence of intolerable adverse events reported by parents/legal guardians or if requested by their parents/legal guardians as a free choice.

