### Statistical analysis, power calculation and sample size

#### Sample size/power

The sample size calculation is based on primary outcome assumption in the intervention and control group. The primary outcome is the improvement of severity level of ASD symptomatology, measured with ADOS-2 which defines the existence of a responder. A recent study carried out by our group gives as an expected rate of responder equal to 62 % [80].

Sample size calculations were performed using the nQuery advisor 6.2 software, based on the primary efficacy variable. Assuming a response rate of 62 % in the placebo group and 90 % in the probiotic group, it was calculated that 38 patients per treatment arm would be sufficient to achieve 90 % power in detecting a treatment difference based on 1-tail w2 test at a significance level of 0.05. Therefore a number of 50 subjects to be enrolled per group was considered sufficient to reach the goal accounting for a certain degree of drop-out rate reported in previous studies on the effects of probiotics [34, 54–56].

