#### Data and statistical analysis

All data were will be collected and analyzed independently of the investigators, who will not have access to the data or to its analysis until the latter had been completed. Baseline and demographic data will be tested for balance between treatments using a 1-way analysis of variance (ANOVA), w2 test, or Fisher exact test, as appropriate. As designed by the protocol, the primary comparison for efficacy will be the responder rate according to ADOS 2 score; the analysis will be carried out on the intent-to-treat population, defined as all randomized patients who received at least one dose of study medication. Dropouts will be considered as no responders. Comparison between treatment groups will be carried out by Cochran/Mantel/Haenszel test for responder counts, controlled for basal value, on either the total population of enrolled patients and on the subset of patients completing the treatment. Post hoc-trend analysis of responders within each group will be carried out by the Cochran-Armitage trend test. All data will be analyzed by means of SAS 8.2 Stat Procedures.

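### The increase from 38 to 50 per arm preserves 90% power only if dropouts leave the analysis; the primary comparison counts them as non-responders, and its power falls below 90% once dropout exceeds about 7%

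*Protocol article*

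**What the plan says.** In the protocol article, the Sample size/power section sets the design assumptions: "Assuming a response rate of 62 % in the placebo group and 90 % in the probiotic group". It concludes that "38 patients per treatment arm would be sufficient to achieve 90 % power", "based on 1-tail w2 test at a significance level of 0.05". The target is then raised: "50 subjects to be enrolled per group was considered sufficient to reach the goal accounting for a certain degree of drop-out rate". The section refers to earlier probiotic studies for the dropout but prints no rate.

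The Data and statistical analysis section says that "the primary comparison for efficacy will be the responder rate according to ADOS 2 score". It runs this comparison on an intent-to-treat population of randomised children who took at least one dose, and adds: "Dropouts will be considered as no responders". It also plans the same test on the children who complete treatment.

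The Participants section gives the total: "We aim to enroll 100 preschoolers with ASD". Allocation is 1:1 between probiotic and placebo within each GI stratum (Interventions; Assignment of interventions). Table 1 schedules ADOS-2 only at baseline and at 6 months.

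**The concern.** Adding 12 children per arm so that enough remain after losses is the standard correction when a lost child contributes nothing to the analysis. Under the stated primary rule, a child who takes a dose and later leaves contributes a failure. Because ADOS-2 is repeated only at 6 months, anyone who leaves before then has no later primary measurement and falls under that rule. If a fraction d leaves each arm, the analysed rates become 0.62(1−d) and 0.90(1−d), and the difference becomes 0.28(1−d). Extra enrolment sized for removed children does not offset that dilution.

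What is at stake is the meaning of the 90% figure. If real power is lower, the chance of missing the assumed effect exceeds the 10% that the plan implies, and a null primary result could be read as stronger evidence against an effect than the design supports. The Discussion itself names family adherence and the relatively long treatment period as possible limitations, so dropout is not a remote matter here.

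**Working it through.** **Inputs.** Rates 0.62 and 0.90, one-sided α = 0.05, 90% power, 38 per arm, 50 per group (Sample size/power); total 100 (Participants); 1:1 allocation (Interventions); dropouts as non-responders (Data and statistical analysis).

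**Formula.** Two-proportion test with pooled variance under the null, no continuity correction, p̄ = (p1+p2)/2:

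n = [1.645·√(2p̄(1−p̄)) + 1.282·√(p1(1−p1)+p2(1−p2))]² / (p2−p1)²

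Power = Φ{[(p2−p1)√n − 1.645·√(2p̄(1−p̄))] / √(p1(1−p1)+p2(1−p2))}

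**Step 1: the plan's own figure.** p̄ = 0.76; √(2·0.76·0.24) = 0.604; √(0.62·0.38+0.90·0.10) = 0.571. So n = (0.993+0.731)²/0.28² = 37.9, that is 38 per arm. Power at 38 is 90.0%. The stated figure reproduces.

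**Step 2: the implied dropout.** 1 − 38/50 = 24%, since 38/0.76 = 50. This is back-calculated and appears nowhere in the document.

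**Step 3: dropouts removed.** At 24% loss, 38 of 50 remain, the rates stay at 62% and 90%, and power is 90.0%. This is the completer comparison, and for it the increase is correct.

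**Step 4: dropouts as non-responders.** All 50 per arm stay in, with both rates multiplied by (1−d). At d = 24%: p1 = 0.4712, p2 = 0.684, difference 0.2128, p̄ = 0.5776. The numerator is 0.2128·√50 − 1.645·0.6985 = 0.356 and the denominator is 0.682, so power = Φ(0.52) = 69.9%. Exact enumeration of the uncorrected chi-square test gives 69.2%.

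| Dropout, each arm | Analysed rates | Power at 50 per arm, one-sided 0.05 | n per arm for 90% |
|---|---|---|---|
| 0% | 62.0% vs 90.0% | 95.8% | 38 |
| 5% | 58.9% vs 85.5% | 91.7% | 47 |
| 10% | 55.8% vs 81.0% | 86.6% | 57 |
| 15% | 52.7% vs 76.5% | 80.8% | 68 |
| 20% | 49.6% vs 72.0% | 74.8% | 80 |
| 24% (inferred) | 47.1% vs 68.4% | 69.9% | 91 |
| 30% | 43.4% vs 63.0% | 62.8% | 110 |

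Power equals 90% at d = 6.8% and is lower beyond that.

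**Step 5: unequal dropout.** Keep the average at 24%. With 29% loss on placebo and 19% on probiotic, the rates are 44.0% and 72.9% and power is about 91%. With 19% on placebo and 29% on probiotic, they are 50.2% and 63.9% and power is about 40%.

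**The case against.** The strongest reply is that the plan never says 24%. Fifty may be a round number that gives a total of 100, and at 5% dropout the primary comparison still has about 92% power. This stands. A reader might infer that the trial has 70% power at its own planned dropout rate, but the document does not support that, because it names no rate. Only the range can be reported, with 24% labelled as inferred.

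Second, the 62% comes from an earlier study that is not at hand. If its denominator already counted losses as failures, and the 90% was set the same way, multiplying by (1−d) would count dropout twice. This stands as an assumption to declare. The increase itself points the other way: if the rates already absorbed dropout, 38 enrolled would suffice and nothing would need adding.

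Third, the result depends on equal dropout, as step 5 shows. This also stands.

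Fourth, the plan also tests completers, for whom the increase works. That gives the increase a purpose, but the primary efficacy comparison is tied to the intent-to-treat population, so the mismatch remains there.

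Fifth, 50 per group could refer to the GI and NGI strata, since packages are numbered 1 to 50 in each. With 1:1 allocation within strata, the pooled comparison is still 50 versus 50.

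A reader might also take this as an arithmetic error in the protocol. It is not: 38 is correct for its inputs. Nor does it touch type I error, and a null result should in any case be read from its confidence interval.

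**Conclusion.** The concern holds as an inconsistency between the sample-size and analysis sections. The stated 90% is not delivered by the primary comparison once dropout exceeds about 7%. At the inferred ceiling of 24%, the chance of missing the assumed effect is about 30% rather than 10%.

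This rests on four assumptions: 62% and 90% are rates among assessed children; dropout is equal in both arms; 50 per group means 50 probiotic versus 50 placebo pooled over the strata; and the test is the unstratified one-sided 0.05 chi-square test of the sample-size section. The planned Cochran-Mantel-Haenszel test controlled for baseline could shift power somewhat, by an amount that the document gives no basis for estimating.

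**What to change.** In the Sample size/power section, state the assumed dropout rate and restate power for the primary rule. For example: with 50 per arm, dropouts counted as non-responders, equal dropout in both arms and a one-sided 0.05 test, power is about 92%, 87%, 75% and 70% at 5%, 10%, 20% and 24% dropout; 90% power at 24% dropout applies only to the completer comparison. Say as well that 62% and 90% are rates among assessed children, if that is so.

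Keep the non-responder rule. Replacing the primary analysis to rescue a power figure, with recruitment under way, would be a larger change than the problem warrants. Restoring 90% at 24% dropout by enrolment would need about 91 per arm (182 in total), which is not proposed. The cost is one revised statement with a less favourable number, and no additional children. It should be made before unblinding.

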**Fig. 1 Fig1:**
[figure not shown]
Flow-chart of the phases of the RCT. Legend: ASD: Autism Spectrum Disorders, DSM-5: Diagnostic and Statistical Manual of Mental Disorders-5th Edition, T0: Time 0, T1: Time 1, T2: Time 2, GI: Gastro Intestinal, NGI: Non-Gastro Intestinal ADI-R: Autism Diagnostic Interview-Revised, ADOS-2: Autism Diagnostic Observation Schedule- Second Edition, CARS: Childhood Autism Rating Scale, RBS-R: Repetitive Behavior Scale-Revised, SCQ: Social Communication Questionnaire, GI Severity Index: Gastro Intestinal Severity Index, CBCL 1.5-5: Child Behavior Checklist 1.5-5, PSI: Parenting Stress Index, VABS-II: Vineland Adaptive Behavior Scale-Second Edition, CDIs: MacArthur-Bates Communicative Development Inventories, GMDS-ER: Griffiths Mental Development Scale-Extended Revised, LPS: Lipopolysaccharide, TNF–α: Tumor Necrosis Factor-α, IL-6: Interleukin-6, PAI–1: Plasminogen Activator Inhibitor-1, EEG: Electroencephalography.

#### Data and statistical analysis

All data were will be collected and analyzed independently of the investigators, who will not have access to the data or to its analysis until the latter had been completed. Baseline and demographic data will be tested for balance between treatments using a 1-way analysis of variance (ANOVA), w2 test, or Fisher exact test, as appropriate. As designed by the protocol, the primary comparison for efficacy will be the responder rate according to ADOS 2 score; the analysis will be carried out on the intent-to-treat population, defined as all randomized patients who received at least one dose of study medication. Dropouts will be considered as no responders. Comparison between treatment groups will be carried out by Cochran/Mantel/Haenszel test for responder counts, controlled for basal value, on either the total population of enrolled patients and on the subset of patients completing the treatment. Post hoc-trend analysis of responders within each group will be carried out by the Cochran-Armitage trend test. All data will be analyzed by means of SAS 8.2 Stat Procedures.

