### Assignment of interventions

After inclusion in the study and baseline assessment, participants will be assigned to the GI group or to the NGI group depending on their baseline scores at the GI Severity Index [60], as previously described. Then, participants of these two groups will blind receive a treatment with probiotics or with placebo according to a computer generating randomization sequence previously determined by the company supplying probiotic and matched placebo. The allocation ratio of intended numbers of participants will be 1:1 both in the GI and in the NGI comparison groups so that the number of children receiving probiotics or placebo will be identical respectively in the two GI and in the two NGI groups.

Randomization will be made in blocks with random sequences of independent block both in the GI and in the NGI groups; the order of interventions will be vary randomly within each block, so that the assignment blocking schedules will be unpredictable. The study will be double blind till its conclusion, so that subjects, caregivers, all research investigators and all the outcomes assessors will be blinded to treatment group assignment of all subjects till the end of data collection and analysis.

The packages containing probiotics will be indistinguishable from those containing placebo and will be enumerated progressively in the two clinical subgroups (GI: from 1 to 50; NGI from 1 to 50). The allocation sequence will be concealed and the matching between the randomization number and the contents of each package (probiotics or placebo) will be written in sealed envelopes (one for each recruited subject/randomization number) stored at the Institute of Clinical Physiology National Research Council (Pisa, Italy).

The research investigators will assign a number of treatment to each of the recruited children on the basis of their respective progressive order of enrollment inside each of the two subgroups. So, the first child enrolled in the GI subgroup will receive the treatment packages labelled “GI1”, the second child enrolled in the GI subgroup will receive the treatment packages labelled “GI2”, the first child enrolled in the NGI subgroup will receive the treatment packages labelled “NGI1” and so on.

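### The primary Cochran-Mantel-Haenszel test omits GI/NGI, the factor on which randomisation is stratified; if GI status predicts response, the test is conservative and loses a little power

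*Protocol article*

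**What the plan says.** Under Assignment of interventions, children are first classified as GI or NGI and then randomised within that class: "Randomization will be made in blocks with random sequences of independent block both in the GI and in the NGI groups". Allocation is 1:1 in each class, and treatment packages are numbered 1 to 50 in each.

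Under Data and statistical analysis, the primary comparison is the ADOS-2 responder rate. It is tested by a "Cochran/Mantel/Haenszel test for responder counts, controlled for basal value", on all enrolled patients and again on those completing treatment. The baseline value is not defined further; in context it most naturally means the baseline ADOS-2 score. No other control variable is given.

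Under Sample size/power, the trial is sized without any stratification: "Assuming a response rate of 62 % in the placebo group and 90 % in the probiotic group", by a "1-tail w2 test at a significance level of 0.05". The article concludes that "38 patients per treatment arm would be sufficient to achieve 90 % power" and that "a number of 50 subjects to be enrolled per group was considered sufficient".

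**The concern.** Blocking within GI and NGI forces the two arms to be balanced on GI status. If response differs between the strata, that balance makes the difference between arms vary less than a test that ignores the stratum assumes. The standard error is then too large, the actual type I error falls below the nominal level, and some power is lost.

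This is more than a detail left to an unseen analysis plan, because the article names the control variable and the one it names is not the randomisation factor. At stake is a little efficiency in the primary test, and a possible later argument about whether the stratum was added after the data were seen.

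**Working it through.** **Inputs from the article**
- Response 62% on placebo and 90% on probiotic; one-sided α = 0.05; 90% power with 38 per arm; 50 enrolled per group (Sample size/power).
- GI and NGI packages numbered 1 to 50 each, 1:1 within each (Assignment of interventions). I read this as 50 per treatment arm, with 25 per arm in each stratum.

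**Assumption.** The article gives no responder rate by stratum. I set the placebo rates at 62% − d and 62% + d and vary d from 0 to 0.30, so the gap between strata is 2d.

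**Step 1: the plan's own figure.** For two proportions with pooled variance and no continuity correction,

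n = [z(0.95)·√(2·p̄·(1 − p̄)) + z(0.90)·√(p₁(1 − p₁) + p₂(1 − p₂))]² / (p₂ − p₁)²

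with p̄ = (0.62 + 0.90)/2 = 0.76:
- 1.645 × √(2 × 0.76 × 0.24) = 1.645 × 0.604 = 0.993
- 1.282 × √(0.2356 + 0.0900) = 1.282 × 0.571 = 0.731
- n = (0.993 + 0.731)² / 0.28² ≈ 37.9, so 38 per arm, with power 90.04%

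The stated figure reproduces. Adding the stratum does not change it.

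**Step 2: why the unstratified test is conservative.** With equal strata and exact 1:1 allocation in each, the true null variance of the difference is smaller than the pooled variance by the factor

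1 − d² / (0.62 × 0.38)

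This is 1 at d = 0, 0.958 at d = 0.10, 0.830 at d = 0.20 and 0.618 at d = 0.30. It never exceeds 1, so the type I error can only move downwards, apart from small effects of discreteness.

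**Step 3: size at the planned rates.** I compared a Mantel-Haenszel test ignoring GI/NGI with one stratified by it, using 400,000 simulated trials per setting. A common odds ratio was chosen to give a mean of 90% on probiotic. All entries are one-sided at 0.05, shown as without / with the stratum.

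| Gap between strata (2d) | Type I error, 50 per arm | Power, 50 per arm | Power, 38 per arm |
|---|---|---|---|
| 0 points | 0.048 / 0.049 | 96.4% / 96.4% | 90.9% / 91.0% |
| 20 points | 0.045 / 0.052 | 96.6% / 96.8% | 91.3% / 91.8% |
| 40 points | 0.035 / 0.050 | 97.2% / 97.8% | 92.3% / 93.8% |
| 60 points | 0.017 / 0.050 | 98.1% / 98.9% | 94.0% / 96.0% |

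The one-sided loss is 0 to 0.8 points at 50 per arm and 0 to 2.1 points at 38 per arm. A full enumeration of outcomes at the four gaps shown agrees with the simulation to within rounding and simulation error.

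**Step 4: a less favourable case.** Placebo response is taken as 77% in one stratum and 47% in the other (a 30-point gap), with gains of 20 and 28 points, 25 per cell. The mean gain is (20 + 28)/2 = 24 points, below the planned 28.
- Two-sided type I error: 4.0% without the stratum, about 5.0% with it.
- Two-sided power: about 81% without, 84% with, a loss of 2 to 3 points.
- One-sided power: 89.1% without, 90.7% with.

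**Limits.** Neither step models the planned control for baseline. Dropout is not modelled either; "Dropouts will be considered as no responders" keeps such children in the denominator and lowers the rates. The 38-per-arm column corresponds to a completer analysis with 12/50 = 24% lost.

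**The case against.** The strongest reply is that these comparisons do not test the planned analysis. The comparator ignores all covariates, whereas the plan already controls for the baseline value. The article's Discussion links GI symptoms to autism severity in an earlier study, and a test that controls for baseline ADOS-2 may capture part of that link. This stands: the losses shown may be overstated.

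A reader might infer that the trial's own hypothesis makes GI status prognostic. The text does not go that far. The Objectives describe a possible endophenotype, and the Discussion expects GI children on probiotic to do better than GI children on placebo. That concerns the treatment effect within GI; nothing says that GI status predicts ADOS-2 response on placebo.

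A reader might also infer that an error rate that departs from nominal puts the efficacy claim at risk. It does not, since the departure is only downwards.

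Nor does the text show that the baseline control will produce sparse strata. It does not say that each score level forms a stratum, and how the score is grouped is commonly left to the analysis plan.

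What survives is the mismatch itself: the article fixes a control variable and leaves out the randomisation factor.

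**Conclusion.** The point holds as a modest improvement to the primary analysis. The test as written does not reflect the stratified randomisation. If GI status does not predict response, the omission costs nothing. If it does, the test is conservative, with a power loss under 1 point one-sided at the planned rates and 50 per arm, and about 2 to 3 points two-sided in the assumed 30-point case.

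The size rests on assumed gaps between strata, on equal strata of 50, on no dropout, and on a comparator without the planned baseline control. It also reads 50 per group as 50 per treatment arm pooled over GI and NGI. If the primary comparison were instead made within each stratum at 25 per arm, the adjustment would not arise; one-sided power would then be about 76%, which is a separate question.

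**What to change.** State that the primary Cochran-Mantel-Haenszel test is stratified by GI/NGI and by baseline ADOS-2 in a small number of prespecified categories. Keep the baseline control: replacing it with GI/NGI would be a trade-off, since the baseline score may be at least as prognostic. If change in ADOS-CSS is analysed, as the Primary outcome measure section suggests, use ANCOVA with baseline CSS and GI/NGI.

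The categories should be coarse because crossing many score levels with GI/NGI wastes information. Assuming ten equally filled, non-prognostic levels and 62% versus 90%, one-sided power falls from 96.4% unstratified to 94.9% with score levels alone and 92.8% when they are crossed with GI/NGI.

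No new data are needed, because every child is classified at T0. The costs are a coarser baseline adjustment and a protocol wording change, which under Data monitoring may need authorisation from the Ethics Committee and the Ministry. It should be made before unblinding.
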